**QRI data analysis**

All qualitative interviews will be audio-recorded using digital encrypted recorders, transcribed verbatim, and edited to ensure anonymity. Audio-recordings will be transcribed by internal University of Bristol staff or an external transcription company which has signed the necessary University of Bristol confidentiality agreements. Transcripts will be pseudo-anonymised. Interview data will be managed using NVivo software (QRS International) and analysed thematically using constant comparative approaches adopted from Grounded Theory. Audio-recorded recruitment consultations and follow up discussions will be subjected to content, thematic, and novel analytical approaches, such as targeted conversation analysis. There will be a focus on aspects of information provision that are unclear, disrupted, or potentially detrimental to recruitment and/or adherence. Standard approaches to enhancing rigour, such as double-coding, triangulating, and seeking out ‘negative cases’, will be employed throughout.

# Eligibility criteria

## Main trial criteria

### Inclusion criteria

- Age ≥18 years (no upper age limit)
- Presence of symptomatic PAD (tissue loss and/or rest pain and/or lifestyle limiting claudication)
- Severe aorto-iliac occlusive PAD defined as “Inter-Society Consensus for the Management of Peripheral Arterial Disease” (TASC II) class C or class D diagnosed on prior cross-sectional imaging
- Patient discussed in any local vascular Multi-Disciplinary Team (MDT) meeting/discussion and deemed suitable for open surgery or endovascular treatment.
- Patient willing and able to give consent and commit to study follow-up.
- An ability to understand written English or availability of a translator to explain the trial documentation

### Exclusion criteria

Asymptomatic PAD

## Communication study (patients) criteria

### Inclusion criteria

- Patient willing and able to give consent
- An ability to understand written English or availability of a translator to explain the study documentation
- Involved with research visits with nurses and/or doctors that have provided consent for the HCP Communication Study (where related to audio-recording of research visits)

## Communication study (healthcare providers) criteria

### Inclusion criteria

- Willing and able to give consent
- Involved with research visits with patients that have provided consent for the Communication Study (where related to audio-recording of research visits)

**PLEASE NOTE: Participants must meet all eligibility criteria to be considered for the EVOCC trial. There are NO eligibility waivers.**

# Trial Interventions

## Open surgery

Open surgical revascularisation is an established treatment strategy for patients with symptomatic PAD and aortoiliac occlusive disease in the NHS. The exact configuration of the open surgical revascularisation will be left to the clinicians who offer the treatment at each site. Such procedures include aorto-(bi/uni)-femoral/iliac bypass, femoro-femoral crossover, axillo-femoral bypass (unilateral or bilateral), aortic endarterectomy, iliac endarterectomy (unilateral or bilateral) or a combination of these procedures. Inflow and outflow procedures, both open and endovascular, will be allowed and left at the discrepancy of the treating clinicians/centres (e.g., concomitant endarterectomy or any form of adjunct endovascular procedure deemed necessary locally).

## ENDOVASCULAR TREATMENT

Endovascular treatment is an established treatment strategy for patients with symptomatic PAD and aortoiliac occlusive disease in the NHS. The exact type of procedure offered to each patient will be decided locally, based on clinicians’ preferences and patient characteristics. Any type of angioplasty device, stent, vessel preparation strategy, or other adjunct endovascular procedure can be used, at the discretion of the clinicians at each trial site. Inflow and outflow procedures, including open surgical access to arteries or open surgical reconstruction to ensure adequate inflow/outflow will be allowed.

For both open surgery and endovascular treatment, inflow and outflow procedures (e.g. adjunct open surgery when undergoing endovascular treatment or vice versa) will be left to the treating clinicians to decide/offer.

# TRIAL PROCEDURES

## Participant identification and recruitment for pilot and main RCT

The Trial Schema () demonstrates the recruitment process in addition to the treatments and follow-up schedule. The recruitment phase will commence as soon as there is ethical, research governance and regulatory approval, local site capacity and capability and only after the Sponsor green light has been issued.

Potentially eligible participants are identified by the clinical care team through surgical waiting lists, clinics (elective or emergency), on calls, or by the patient’s direct clinical care team; they will be discussed at vascular team meetings to confirm eligibility and suitability to take part in the trial. This allows staff to identify patients with consent capacity issues early.

Following identification by the clinical team, the patients will be approached by a delegated member of the clinical team. The potential participant will be provided with the Participant Information Sheet (PIS) either in person, by post, or via e-mail (as per their preference).

## Consent

The Principal Investigator (PI) retains overall responsibility for the conduct of research at their site, this includes the taking of informed consent of participants at their site. They must ensure that any person delegated responsibility to participate in the informed consent process is duly authorised, trained and competent to participate according to the ethically approved protocol, principles of Good Clinical Practice (GCP) and Declaration of Helsinki. If delegation of consent is acceptable then details should be recorded in the Delegation of Authority Log.

Telephone, electronic or written informed consent must be obtained prior to the participant undergoing procedures that are specifically for the purposes of the trial and are out-with standard routine care at the participating site (including the collection of identifiable participant data).

The right of a participant to refuse participation without giving reasons must be respected.

The option of electronic consent and telephone consent has been developed as an alternative to face-to-face methods. This model has been developed where it is not in the best interests of the patient to bring them back to hospital for research purposes, the patient does not want to or are unable to come into the hospital. It is anticipated that the majority of potential participants will wish to have a face-to-face visit. The electronic consent process will mirror the content of the paper documents, including an electronic PIS, and will be supported by the REDCap platform provided by Biomedical Research Centre Health Informatics. This will be supported by a Video/Telephone Consent Form to be completed by the researcher or delegated site person performing consent, confirming that the participant has understood the information and consent process. The electronic consent system will only be accessible by appropriate personnel active on the study who will only be able to view consents for their site. The system will notify of any errors in a submitted consent form which can be rectified by the participant, as well as produce a PDF for the participant, research and medical records. Where appropriate, electronic consent will be supported either over the telephone or by video conference between the participant and the clinician/researcher. The remote consent process will also mirror the content of the paper documents. The Video/Telephone Consent Form will be completed by the researcher or delegated site person receiving informed consent, confirming that the participant has understood the information and has capacity to consent. The remote consent process will only be performed by delegated personnel at each site.

The participant must remain free to withdraw at any time from the trial without giving reasons and without prejudicing his/her further treatment and must be provided with a contact point where he/she may obtain further information about the trial. Data collected up to the point of withdrawal will be retained and used. Where a participant is required to re-consent or new information is required to be provided to a participant it is the responsibility of the PI to ensure this is done in a timely manner.

A Participant Information Sheet (PIS) will be provided to facilitate this process. The Principal Investigator or their delegate will ensure that they adequately explain to the participant the aim, trial intervention, anticipated benefits and potential risks of taking part in the trial.

The participant will be given time to consider the information, and the opportunity to question the Investigator, their GP or other independent parties to decide whether they will participate in the trial. They will be given sufficient time, usually 24 hours, to make their decision. Written Informed Consent will then be obtained by means of participant dated signature and dated signature of the person who presented and obtained the informed consent. The person who obtained the consent must be suitably qualified and experienced, and have been authorised to do so by the Principal Investigator as detailed on the Delegation of Authority and Signature log for the trial. The original signed form will be retained at the trial site within the Investigator Site File (ISF). A copy of the signed Informed Consent will be given to participants and a copy retained in the participant medical notes. The outcome of the conversation, i.e., provided informed consent and have been randomised to the trial, will be recorded in the trial screening log. This will be necessary for assessing recruitment feasibility.

The ICF contains optional items relating to consent for the use of data held by central NHS bodies (see below) and the retention of contact information to enable future contact for consideration of participation in follow-up studies. Participants may provide or decline consent for any of these items independently. Should new and important information, particularly relating to safety, become available during the trial, participants may be required to re-consent to the trial via an updated PIS and ICF.

Once the participant is randomised onto the trial, their Participant ID Number will be populated and recorded on the ICF and all Case Report Forms (CRFs) going forward.

Details of the informed consent discussions should be recorded in the participant’s medical notes in accordance with Good Clinical Practice (GCP). This should include date of discussion, the name of the trial, outcome of the discussion, version number of the PIS given, version number of ICF signed and date consent received.

### Optional consent for linkage of NHS routine clinical datasets

EVOCC includes an optional consent to allow linkage to patient data available in NHS routine clinical datasets, such as the Hospital Episode Statistics (HES) and mortality data from the Office of National Statistics (ONS) through The Health and Social Care Information Centre and other central UK NHS bodies. This consent will also allow access to other new central UK NHS databases that may appear in the future so that relevant long-term outcomes and health resource usage data can be recorded to extend the follow-up of participants without needing to contact them further. This is important as it will link treatments that may become a clinical standard of care to long-term outcomes that are routinely collected in clinical data, but which will not be collected during the follow-up period of the trial.

## Randomisation

After the consent form has been signed, the participant will be randomised to receive one of the two arms; open surgery or endovascular treatment. Participants will be randomised via the 24 hour, web-based service, Sealed Envelope.

Random allocations will have a 1:1 ratio, will be minimised by the following variables: age above 65 years, sex, and presence of tissue loss (yes/no) and stratified by site. Randomisation forms should be completed alongside online randomisation. After a participant is randomised, the user is presented with the allocated treatment group and the unique Participant ID Number. A notification email will be sent to the person conducting the randomisation, copying in Leicester Clinical Trials Unit via the EVOCC trial mailbox. The Participant ID number must be entered onto the participant signed ICF and all CRFs from this point forward and will link the participant details to the trial data. Any errors in the randomisation process should be reported to Leicester Clinical Trials Unit as soon as reasonably possible after being identified.

## Trial assessments

### Baseline Visit (Day 0)

Once a Participant ID Number is allocated, the Baseline visit can take place. During this visit, participants will complete participant questionnaires, undergo a review of their medical history (including previous surgical interventions), cardiovascular risk factors, PAD anatomy, eGFR, HbA1C, LDL and cholesterol levels. If a female is thought to be pregnant, a urine pregnancy test will be performed as part of usual care ahead of surgery. Where a female participant is found to be pregnant, progression to treatment will be assessed using a risk-based approach as managed routinely by the patient’s treating clinician. Baseline visit biochemistry assessments/bloods to be taken in line with clinical pathway and matching the research schedule as closely as possible. It is understood that because these bloods are clinical, that there may be occasions where these bloods are taken ahead of the research baseline timepoint. Please refer to **Table 2** for further details about the Baseline visit, follow up visits and assessments.

### Review of Clinical Events – Day of Discharge, Day 30 and Months 6, 12, 24, 36, 48 and 54

A review of clinical events, particularly those related to the cardiovascular system, will be undertaken at the above trial visits including re-intervention, admission to hospital, death, myocardial infarction, stroke and new heart failure leading to admission. For visits at day 30, months 12, 36, 48 and 54, data collection will be performed either by telephoning the participant or retrieving the information from their medical notes. For visit month 6, the participant needs to attend clinic in person. However, if the participant cannot attend in person, as this is a pragmatic study this information can instead be collected remotely via telephone or through acquiring information through participant medical records.

### Biochemistry Assessments – Baseline and Month 6

Standard blood sample assessments to be undertaken in clinic at Baseline and month 6 and should include eGFR, total cholesterol, LDL cholesterol and HbA1C - these are NHS standard of care and constitute part of these patients regular care as per NHS and National Institute for Health and Care Excellence guidance. The blood samples (5ml collected at each visit) will be collected at room temperature before being processed and analysed at the local pathology laboratories as per each site’s standard procedures for these patients.

### Ankle Brachial Pressure Index (ABPI) – Baseline and Months 6, 12, 24, 36, 48, 54

ABPI is a reliable way to detect arterial insufficiency and is the ratio of the ankle systolic blood pressure to the brachial systolic blood pressure. It will be measured using a sphygmomanometer and a hand-held Doppler device by appropriately trained personnel e.g., a research nurse or a clinician. This constitutes part of these patients regular care as per NHS and National Institute for Health and Care Excellence guidance.

An ABPI ratio of:

- < 0.5 suggests severe arterial disease
- > 0.5 to < 0.8 suggests the presence of arterial disease or mixed arterial/venous disease
- Between 08 – 1.3 suggests no evidence of significant arterial disease
- > 1.3 may suggest the presence of arterial calcification

Measurements at 30 days and months 6, 12, 36, 48 and 54 can be taken from the participant’s medical records.

### EuroQOL 5D 5L Questionnaire – Baseline and Months 6 and 12

EuroQOL- 5D (EQ-5D-5L) is a standardised assessment of health status to provide a simple, generic

measure of health for clinical evaluation (10, 11). It consists of 2 pages covering 5 dimensions (mobility, self-care, usual activities, pain/discomfort and anxiety/depression) and the participant is

asked to choose an accompanying statement which best describes how much ease or difficulty they

have in each of these dimensions (1 is scored as no problems/pain/anxiety/depression, 5 is scored as

unable to/extreme anxiety/depression). The questionnaire also asks the participant to indicate on a scale of 1-100 1 = the worst health you can imagine, 100 = the best health you can imagine how their health is on that day.

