# BACKGROUND

The clinical and cost-effectiveness of open surgery vs. minimally invasive endovascular treatment for severe occlusive aortic and iliac artery disease is unknown. This area has been identified as a research priority in a recent James Lind Alliance (JLA) process across several vascular disease areas, such as peripheral arterial disease (PAD), diabetic foot care, and amputations (1).

Lower limb Peripheral Arterial Disease (PAD) affects 20% of people over 55 years of age (2) and is the main cause of amputations in the NHS (2). Often, patients with PAD develop leg pain when walking (called claudication). Some patients might also develop leg pain at rest or lower limb necrosis, a condition called Chronic Limb Threatening Ischaemia (CLTI) (3). This is limb and life threatening and requires urgent revascularisation to save the patient’s limb/life (3). The aorta and iliac arteries are common sites affected in people with lifestyle limiting claudication or CLTI (4). These patients can have revascularisation either with open surgery or more recently developed minimally invasive techniques in the form of endovascular treatment (3). Both open surgery and endovascular treatment, however, are associated with significant complications. Open surgery is associated with a 3% early mortality and many perioperative complications (5). Endovascular treatment is less invasive, with a 1% early mortality rate (5, 6). Endovascular devices, however, are costly and 43% of patients need re-intervention within 3 years (5).

Patients in our study development focus groups expressed a preference for endovascular treatment. They were, however, concerned about the many re-interventions and high number of late deaths or amputations potentially associated with endovascular treatment. Some patients even voiced concerns about the high cost of the endovascular devices and many re-interventions. There is no randomised evidence comparing the clinical and cost-effectiveness of these techniques in this context, potentially leading to more deaths, amputations, and increased NHS costs. Clinicians therefore do not know which treatment to offer this cohort. The need to improve outcomes and reduce amputations in CLTI/claudication has been highlighted by the JLA and Vascular Society of Great Britain and Ireland (VSGBI) in 2021 as a key research priority (1).

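### Baseline EQ-5D-5L is scheduled after randomisation has shown the arm, so knowledge of the allocation may affect it and, through it, the QALY comparison

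*Protocol*

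**What the plan says.** The order of events has to be put together from several sections of the protocol.

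- **Consent, then randomisation.** Section 8.3: "After the consent form has been signed, the participant will be randomised to receive one of the two arms". Section 5 likewise has randomisation follow directly on written consent.
- **Arm and number appear together.** Section 8.3: "After a participant is randomised, the user is presented with the allocated treatment group and the unique Participant ID Number". Section 8.2 confirms that the number does not exist before then: "Once the participant is randomised onto the trial, their Participant ID Number will be populated".
- **Baseline visit next.** Section 8.4.1: "Once a Participant ID Number is allocated, the Baseline visit can take place". On its content: "During this visit, participants will complete participant questionnaires, undergo a review of their medical history (including previous surgical interventions), cardiovascular risk factors, PAD anatomy".
- **EQ-5D-5L belongs to baseline.** The heading of Section 8.4.5 reads "EuroQOL 5D 5L Questionnaire – Baseline and Months 6 and 12". Table 2 puts EQ-5D-5L, ABPI and arterial anatomy in the Baseline column.
- **One exception.** Section 8.4.1 accepts that clinical blood samples may have been taken before the research baseline. It gives no such allowance for the questionnaire.
- **No blinding.** The trial summary calls the trial open label, and Section 5 says blinding is not possible.

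Two places do not fit this order. Under QRI consent processes (Section 5.1.1), patients give written consent for audio-recording at the baseline visit and recruitment discussions may continue afterwards, which implies a baseline visit before randomisation. Table 2 lists eligibility check, consent, randomisation and all baseline measures in one Day 0 column without an order.

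**The concern.** A baseline value is useful because randomisation cannot have influenced it. If it is recorded after the arm is known, that guarantee is lost. EQ-5D-5L is the measure most exposed: the participant fills it in, one of its five dimensions is anxiety/depression, and it asks for a rating of health on that day. Being told that one will have open surgery, or that one will not, could change those answers before any treatment is given. The Background makes some reaction plausible: "Patients in our study development focus groups expressed a preference for endovascular treatment".

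What is at stake is the economic evaluation and the quality-of-life outcome. Section 3.2 puts cost-effectiveness in the primary objective, and Section 11.6.5 derives utilities from EQ-5D-5L. The baseline value normally enters a QALY analysis, either as the first point of the area under the curve or as a covariate. A statistical analysis plan written later cannot recover a pre-allocation value that was never collected.

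**Working it through.** **1. The plan's own figure.** No stated number is in dispute. The sample size reproduces: 596 / (1 − 0.05) = 627.4, rounded up to 628 (Section 11.1). The timing of baseline assessments does not enter it.

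**2. The order.** Sections 8.2, 8.3 and 8.4.1 together give: consent → randomisation → arm and Participant ID shown → baseline visit → EQ-5D-5L. Nothing in the protocol withholds the allocation until the questionnaire is complete.

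**3. Which baseline items are exposed.**

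| Item | How allocation could act | Exposure |
|---|---|---|
| EQ-5D-5L | Directly on the participant's answers | Clear |
| ABPI (Section 8.4.4) | Only through an unblinded assessor or a delay before the visit; it is a Doppler pressure ratio | Minor |
| Anatomy/TASC class | Only through how existing images are read and recorded; Section 6.1.1 requires the class from prior cross-sectional imaging, and the subgroups using it (Section 11.6.1) are exploratory and unpowered | Minor |
| Age, sex, tissue loss, site | None; they are needed to run the randomisation | None |

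**4. Size for EQ-5D-5L.** Let b be the amount by which knowing the allocation lowers mean baseline utility in one arm relative to the other, with later utilities unchanged. The documents give no value for b or for the baseline-to-follow-up slope β. I assume b = 0.02 to 0.05 and β = 0.4 to 0.6.

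*Unadjusted area under the curve.* QALYs over months 0 to 6 by the trapezoid rule are 0.5 × (u0 + u6) / 2. Lowering u0 by b changes this by −0.5 × b / 2 = −0.25b.

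- b = 0.02: 0.25 × 0.02 = 0.005 QALY
- b = 0.05: 0.25 × 0.05 = 0.0125 QALY

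The error is **against** the arm with the lower baseline.

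*Baseline-adjusted comparison.* The adjusted difference is (difference in follow-up means) − β × (difference in baseline means). A spurious baseline difference of −b adds +βb at each time point.

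- b = 0.02: 0.4 × 0.02 = 0.008 to 0.6 × 0.02 = 0.012
- b = 0.05: 0.4 × 0.05 = 0.020 to 0.6 × 0.05 = 0.030

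The error is **in favour of** the arm with the lower baseline.

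The first pair is in QALYs over six months and the second in utility per time point, so they are not on one scale. What they show is that the sign of the error depends on the analysis chosen.

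**The case against.** The strongest reply has five parts.

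- **The primary result is untouched.** Death or major amputation does not depend on the baseline visit, and Section 11.5 adjusts only for factors used at randomisation. This stands in full. EQ-5D-5L is a secondary outcome, although it serves a cost-effectiveness question that Section 3.2 places in the primary objective.
- **The text does not say that the participant knows.** Section 8.3 shows the arm to the user of the randomisation system, and no section says when the participant is told. This stands as a limit: influence on the answers is possible, not demonstrated. But no safeguard prevents it.
- **The order may be loose wording.** Section 8.4.1 says the visit can follow, Table 2 places everything on Day 0, and Section 5.1.1 implies an earlier baseline visit. Some sites may therefore collect EQ-5D-5L before randomisation. That would leave timing mixed across sites, which is a further reason to settle it.
- **The direction is unknown.** Right after reporting a preference for endovascular treatment, the Background says the same patients worried about re-interventions and late deaths or amputations with it. Section 2.6 reports that all found randomisation acceptable. This stands: no direction by arm should be claimed.
- **Baseline adjustment is not stated.** Section 11.6 refers back to adjustment already described, which is for the minimisation factors, and Section 11.6.5 mentions no baseline utility. This also stands, so both analyses are shown above.

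A reader might go further and carry a slope of 0.5 over 3 years. That gives 1.5 × 0.02 = 0.03 to 1.5 × 0.05 = 0.075 QALY towards surgery, or 20% to 49% of the 0.153 QALY difference in Section 2.2. The documents do not support this. It needs an adjustment the protocol does not specify, a known direction, a constant slope and no deaths, whereas Section 2.2 itself gives 3-year survival of 65% to 70%. The 0.153 comes from an early decision model on data that the same section calls unadjusted and observational, so it is not a design assumption. The unadjusted analysis gives 0.005 / 0.153 = 3% to 0.0125 / 0.153 = 8%, in the opposite direction.

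**Conclusion.** The point holds for EQ-5D-5L. As written, Sections 8.3 and 8.4.1 place a self-reported baseline after the allocation is on the site's screen, in an open-label trial, with nothing to hold the allocation back. Knowledge of the arm may therefore bias the quality-of-life and QALY comparisons.

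Under the assumed b and β, the error is modest: up to about 0.0125 QALY against the lower-baseline arm if unadjusted, or up to about 0.030 utility per time point in its favour if adjusted. Which arm that would be is not established.

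Two wider readings are not supported. One is that the trial's main comparison is compromised: the primary outcome, its adjustment factors and the sample size are independent of this visit. The other is that ABPI and the anatomical subgroups are equally affected: one is a physical measurement and the other is read from imaging that predates randomisation. The correction is still worth making, because it costs little and a clean baseline cannot be obtained afterwards.

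**What to change.** - **Order.** Amend Sections 8.3 and 8.4.1 so that EQ-5D-5L is completed after consent and before randomisation, under a screening number. For consistency, do the same for ABPI and the anatomy/TASC record. Have the randomisation form confirm that the questionnaire is done.
- **Reconcile.** Bring the QRI consent text in Section 5.1.1, the statement in Section 5 that randomisation follows directly on consent, Sections 8.2 to 8.4.1 and Table 2 into one stated sequence.
- **Participants already enrolled.** Record whether each baseline EQ-5D-5L was completed before or after allocation. Report the EQ-5D-5L and QALY results both with and without baseline adjustment as a sensitivity analysis. Because the two err in opposite directions under the model above, the pair shows how far the conclusion rests on the baseline; it does not restore the missing values. Simply excluding post-allocation baselines is not a workable substitute, since at sites that followed the written order it would remove all of them.

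The cost is an amendment to protocol and CRF wording, a screening number and one timing field. The data, staff and day are the same, and the sample size stays at 628.
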